### Data analysis

The data will be analysed using Stata 10.1 for Windows. During the data collection regular data checks (identify out-of-range answers, inconsistent responses and missing data) will be performed.

In the evaluation of the effectiveness of the intervention programme all analyses will be performed at patient and group level. The data will be analysed using the intention-to-treat principle. This means that patients will remain in the group to which they were randomly allocated at baseline. The patient characteristics will be compared for all groups and, if necessary, we will correct for differences.

The determination of complications is based on the complication registration of the Dutch Society of Medical Specialists (in Dutch: Orde van Medisch Specialisten). The determination of adverse events is based on three criteria; 1) an unintended (physical and/or mental) injury which 2) results in temporary or permanent disability, death or prolongation of hospital stay, and is 3) caused by health care management rather than the patient's disease. To determine whether the injury is caused by health care a six-point scale will be used, causation scores of 4-6 will be classified as adverse events. The preventability of the adverse events will also be measured on a six-point scale, scores of 4-6 will be classified as preventable adverse events. The incidence and mean number of complications and adverse events will be calculated.

The inter-rater reliability of the review process will be expressed as a kappa statistic. This kappa statistic will be calculated for the determination of the presence or absence of complications and adverse events. The records from the reliability study will be used for this analysis, they represent up to 10% of all reviewed patient records.

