## Methods/Design

### Study design

This RCT is set up as a multi-centre intervention study in which hip fracture patients aged 65 years and older will be included. Surgical wards of three hospitals will participate in the intervention groups; one surgical ward in another hospital will serve as a control group. The patients in the control group receive care as usual. A baseline measurement using a retrospective record review study will be conducted. In the following RCT the effects of three different interventions will be compared to usual care, randomisation is at patient level. Within the three intervention wards patients are randomly assigned to one of four intervention groups. The groups will receive the following interventions:

• Group 1: use of SBAR communication tool for nurses in the surgical wards

• Group 2: SBAR and patient safety card

• Group 3: SBAR and information leaflet (bundles) for after discharge

• Group 4: SBAR, patient safety card and information leaflet (bundles) for after discharge

During the study period the morning rounds will be observed once a month in each intervention ward to look at the information transfer and communication between care providers. Two weeks and six months after discharge patients will be interviewed about their recovery and the added value of the interventions. Six months after discharge the records of the included patients will be reviewed to detect possible adverse events and unintended harm. Figure 1 gives an overview of the inclusion and data collection.

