### Participating surgical wards

Because the researchers will frequently have to visit the participating surgical wards during the study, one hospital region in the Netherlands will be chosen for the recruitment. Although the treatment for hip fractures is fairly standardised by means of protocols, we aim to include a surgical ward of each of the three hospital types that exist in the Netherlands; a university, a tertiary medical teaching and a general hospital. A fourth surgical ward in another hospital will be included as a control group. An inclusion criterion for the surgical wards is that they have to treat at least 100 elderly patients with a hip fracture each year. The wards will be recruited by informing already existing contacts within the wards about the study. If the ward agrees to participate an official intake by the researchers will follow. The nurses in the participating wards will be informed about the study during a meeting. In this meeting the interventions and the inclusion process will be explained. For each ward background information will be gathered about the number of patients, treatment procedures and discharge planning. This will make it possible to compare the wards and correct for important differences.

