### Outcome measures

The primary outcome measures in this study are the incidence of complications and adverse events, mortality rate within six months after discharge and functional mobility six months after discharge. Secondary outcome measures are length of hospital stay, quality and completeness of information transfer and patient satisfaction with the instruments.

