### General data collection and follow up

After receiving informed consent a questionnaire will be filled out with patient characteristics and the pre-fracture status of the patient. Information about the status before the fracture will be gathered using the 10-item modified Barthel Index for ADL-functioning [42], the Parker and Palmer pre-fracture mobility score [43], the Short Nutritional Assessment Questionnaire [44] and the Delirium Observation Screening Scale [45]. In addition, information will be gathered about the home situation before admission. Before discharge, the questionnaire will be completed with information about the occurrence of pressure wounds, delirium, urinary tract infections, wound infections, falls during admission and possible risk factors after discharge for these complications.

All included patients will be followed for a period of six months after discharge. During this period two interviews by telephone will be held with all included patients, two weeks and six months after discharge. During these interviews patients will be asked some multiple choice questions about their current residence, physical functioning, use of health care, the occurrence of unexpected events and some open end questions about their experiences during the whole care process. In addition to these interviews, the retrospective patient record review study will be conducted to review the patient record up to six months after discharge. The methods of this record review study will be identical to the baseline measurement described earlier. Again, the reviewers will look for complications, adverse events, the quality of record keeping and written information for the transfers of the patient between the different hospital wards. This second record review study will be used to assess the effect of the complete intervention programme on the possible reduction in complications and adverse events.

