## Discussion

### Strengths and limitations of the study

One of the strengths of this study is the integrated intervention programme that will be implemented in three surgical wards. All three interventions are aimed at improving a different aspect of the care for elderly hip fracture patients. This approach may have more impact than implementing three separate interventions in different situations and could increase the possibility of finding measurable effects in patient outcomes. The randomisation at patient level reduces the influence of the differences between the three wards. In every participating ward the included patients should be equally distributed over the four intervention groups. Another important aspect of this intervention programme is that it focuses on one specific patient group that will increase in the future. The baseline measurement will give insight into the complications and adverse events that affect this patient group. This information will provide valuable insights and possibilities for improving patient safety. Finally, the follow-up of six months enables us to assess the functional recovery of patients and their experiences during those months. These experiences can be used to improve the care after discharge for this patient group and to explore the possibilities for care that is more adapted to their needs.

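### Adjustment depends on baseline differences seen in the data, which gives up precision on six-month mobility and can leave the control-hospital comparison uncorrected

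*Protocol article*

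**What the plan says.** The rule for patient characteristics is in the protocol article, Data analysis: "The patient characteristics will be compared for all groups and, if necessary, we will correct for differences". Ward differences get similar conditional treatment under Participating surgical wards, where ward background data are gathered: "This will make it possible to compare the wards and correct for important differences". Neither sentence says what makes a correction necessary or a difference important.

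The material for a fixed adjustment exists. Under General data collection and follow up, "Information about the status before the fracture will be gathered using the 10-item modified Barthel Index for ADL-functioning", and the same sentence adds a pre-fracture mobility score, a nutritional questionnaire and a delirium scale. The primary outcomes include "mortality rate within six months after discharge and functional mobility six months after discharge". The article does not link the pre-fracture scores to the analysis of any outcome.

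Two kinds of comparison fall under the rule. For the first, "Within the three intervention wards patients are randomly assigned to one of four intervention groups". For the second, "one surgical ward in another hospital will serve as a control group", so that comparison is outside the randomisation.

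**The concern.** A covariate belongs in the model because it predicts the outcome, not because it happens to differ between groups. Between randomised groups a baseline difference is chance. A rule that waits for one will usually leave a strong predictor out, and the estimate is less precise than the collected data allow.

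Ward shows this clearly. Under Strengths and limitations, "In every participating ward the included patients should be equally distributed over the four intervention groups". If that succeeds, ward is balanced across groups 1-4 and a rule based on group differences never calls for it, although it is a feature of the design.

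The control comparison has the opposite problem. Patients of another hospital may truly differ, and a balance check that shows nothing does not make an unadjusted comparison safe. SBAR is given on all intervention wards, so this is the only concurrent comparison that bears on SBAR.

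Because the trigger is undefined, the decision to adjust could also be taken after both the adjusted and unadjusted results are known.

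**Working it through.** **1. The plan's own figure.** Power calculation gives a difference of 5, SD 10, alpha 0.05, power 80% and 64 per group. n = 2 × (1.96 + 0.84)² × (10/5)² ≈ 63. The two-sided t-test version gives 63.8, so 64. With 20% drop-out, 64/0.80 = 80. The figure reproduces. Below I borrow only its standardised difference, 5/10 = 0.5, as an illustration for mobility. Whether a formula for means suits a complication risk is a separate matter.

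**2. Precision available for mobility.** The documents do not give the correlation r between pre-fracture and six-month mobility, so a range is assumed. For a continuous outcome, adjustment leaves a residual variance of 1 − r², and the equivalent gain in patients is 1/(1 − r²).

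| r (assumed) | 1 − r² | 1/(1 − r²) |
|---|---|---|
| 0.4 | 0.84 | 1.19 |
| 0.5 | 0.75 | 1.33 |
| 0.6 | 0.64 | 1.56 |
| 0.7 | 0.51 | 1.96 |

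**3. How much of that the conditional rule keeps.** Simulation: 64 per randomised group, one baseline score, 40,000 trials per setting. The conditional rule is represented, by assumption, as a 5% baseline test with adjustment only if significant. The test fires in about 5% of trials.

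| | r = 0.3 | r = 0.5 | r = 0.7 |
|---|---|---|---|
| Power at 0.5 SD, never adjusted | 80% | 80% | 80% |
| Power, adjusted only if baseline differs | 80% | 81% | 82% |
| Power, always adjusted | 84% | 90% | 97% |
| Type I error, adjusted only if baseline differs | 4.8% | 4.2% | 3.6% |
| Type I error, significance claimed if either analysis gives it | 6.4% | 7.2% | 8.3% |

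**4. How often chance offers a reason to adjust.** With k independent characteristics each tested at 5%, the probability that at least one looks imbalanced under perfect randomisation is 1 − 0.95^k: 19% for k = 4 and 40% for k = 10.

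**5. Control comparison: can the check see a real shift?** For a shift of d SDs, the noncentrality is d × √(n₁n₂/(n₁ + n₂)), and detection at 5% is about Φ(noncentrality − 1.96).

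- d = 0.3, 80 v 80: 0.3 × √40 = 1.90, detected about 47% of the time.
- d = 0.3, groups pooled, 320 v 80: 0.3 × √64 = 2.4, about 67%.
- d = 0.5, 80 v 80: 0.5 × √40 = 3.16, about 88%.

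The shifts are assumed.

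**6. Control comparison: error rates.** Same simulation, no treatment effect, 80 v 80, one covariate shifted by 0.3 SD.

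| Type I error | r = 0.3 | r = 0.5 | r = 0.7 |
|---|---|---|---|
| Never adjusted | 8.7% | 15.7% | 26.1% |
| Adjusted only if baseline differs at 5% | 5.3% | 5.8% | 6.4% |
| Always adjusted | 4.9% | 4.9% | 5.0% |

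The middle row is only mildly raised, because under that rule the unadjusted result is used only when the observed difference is small. It describes one covariate under one strict rule, which the plan does not fix.

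**The case against.** The sentence names no test or threshold, and necessity could be read to include prognostic importance. A covariate list is also something an article may leave to the full protocol or analysis plan. Both points stand, so the 5% pretest above is only one version of the rule and the missing list is not the finding. What remains is the stated trigger: correction follows from comparing groups, and an analysis plan that kept to it would inherit the fault.

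A reader might infer that the rule inflates false positives between randomised groups. It does not if applied as a strict pretest: 3.6-4.8% is conservative. Inflation to 6.4-8.3% needs a choice between results, and the article does not say one will be made.

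A reader might also attach the 8.7-26.1% to the plan's rule for the control comparison. Those figures are for never adjusting. Nor is missed confounding the usual outcome in every case: detection runs from 47% to 88% depending on the shift and on pooling.

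Ward is not simply forgotten, since Participating surgical wards plans a correction. That correction is conditional too.

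The 19-96% gain cannot be read as a gain for the trial. It rests on assumed correlations and on mobility analysed as a continuous outcome, while the six-month instrument is not named and the sample size was set on complications.

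Finally, patient-level adjustment cannot remove differences between hospitals. The questionnaire scores are collected after consent, so the change below does not cover the comparison with the 2007 record review.

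**Conclusion.** The point holds in limited form. Making adjustment depend on observed differences gives up most of the precision that the pre-fracture scores could add on six-month mobility in groups 1-4. In the illustration, power is 80-82% under the conditional rule against 84-97% with fixed adjustment, for r from 0.3 to 0.7. This applies to that outcome only; for complications, adverse events and mortality the gain depends on prognostic strength that the documents do not give.

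Between randomised groups the weakness in error control is the undefined trigger, not pretesting as such. In the control comparison a balance check can miss real confounding, to an extent set by the size of the shift and by whether the groups are pooled.

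The trial remains analysable as planned, but the rule should be changed.

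**What to change.** Replace the sentence in Data analysis with a rule fixed before outcome data are seen:

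- Every comparison among groups 1-4 adjusts for ward and age. The analysis of functional mobility also adjusts for the pre-fracture mobility score and the Barthel Index.
- The comparison with the control hospital always adjusts for a named set of collected prognostic variables, such as age, pre-fracture mobility, Barthel Index and nutritional score. The delirium scale and home situation are also collected, so the choice should be justified. Ward is not in this set because it is aliased with control status.
- These covariates are used whatever the observed balance. Baseline tables are descriptive and do not select covariates.
- The report states that hospital effects stay aliased with control status and that patient-level adjustment cannot remove them.

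The sentence on ward differences under Participating surgical wards should be brought into line. The cost is a few lines of text: ward and age are known, and the scores are already to be collected.

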## Discussion

### Strengths and limitations of the study

One of the strengths of this study is the integrated intervention programme that will be implemented in three surgical wards. All three interventions are aimed at improving a different aspect of the care for elderly hip fracture patients. This approach may have more impact than implementing three separate interventions in different situations and could increase the possibility of finding measurable effects in patient outcomes. The randomisation at patient level reduces the influence of the differences between the three wards. In every participating ward the included patients should be equally distributed over the four intervention groups. Another important aspect of this intervention programme is that it focuses on one specific patient group that will increase in the future. The baseline measurement will give insight into the complications and adverse events that affect this patient group. This information will provide valuable insights and possibilities for improving patient safety. Finally, the follow-up of six months enables us to assess the functional recovery of patients and their experiences during those months. These experiences can be used to improve the care after discharge for this patient group and to explore the possibilities for care that is more adapted to their needs.

The study also has some limitations. First, although the results of previous studies showed that the instruments used in retrospective record review studies are sensitive for identifying adverse events [46,47], there are some important factors that have to be considered. The retrospective patient record review method relies exclusively on the information available in the hospital patient record, this can be insufficient for adverse event determination [13,48]. Also, adverse events revealed after discharge are only found if they result in a readmission or if it is recorded in the outpatient record of the patient. The hospital record is not always complete with the risk of missing important information. A general possible weakness in retrospective review studies is hindsight bias [49]. Knowing the outcome and its severity may influence judgement of causation and preventability. A second limitation of the study is that elderly hip fracture patients suffering from dementia cannot be included into the study due to practical and ethical reasons, which may lead to an underestimation of the experienced problems and therefore the possible effects of the interventions. Some other issues that might influence the outcomes in this trial are the randomisation process, the blinding of patients and the possible effect of the presence of the researcher in the intervention wards. It was mentioned before that randomisation will be on patient level. It is possible that two patients in the same room receive different interventions and expose each other to the interventions. Another possible source of bias is that patients cannot be blinded, they are automatically aware of the intervention group that they will be in as they immediately receive the interventions after inclusion. A third issue is the presence of the researchers on the wards on a regular basis for the observations. Once a month the morning rounds will be observed to assess the effectiveness of the SBAR communication tool, this in itself can increase the use of the tool.

### Feasibility

The feasibility of the study depends on a number of factors. First, we are relying on the nurses to include the patients into the trial as they are the first to know when an eligible patient is admitted to the ward. This way, the inclusion can take place as soon as possible after admission. After a few weeks it will become clear whether this method works or not. If the patients are not included by the nurses, the researchers will take over the inclusion process. Second, the success of the intervention programme will depend on the number of available patients, their decision to participate and the loss to follow-up.

### Relevance of the study

The increasing incidence of hip fractures in vulnerable elderly patients in combination with the complex care process they have to go through, with the risks of sub-optimal communication and unintended events, all contribute to the relevance of this study. This study not only aims to improve clinical communication between care providers and involve the patient more in their own care process but will also generate more knowledge and insight into the nature of adverse events and avoidable harm for this patient group. The combined use of three interventions for improving patient safety in this patient group is an innovative aspect of this study.
